### Outcomes

Study hypotheses relate to maternal and fetal reproductive outcomes that have been previously found to be associated with herbicide concentrations during pregnancy in human or animal studies. The primary outcome of the Heartland Study is gestational age at birth. Key human and animal studies supporting these hypotheses have been detailed in Tables 1 and 2. Maternal outcomes that will be considered are pregnancy loss, preterm birth, hypertensive disorders of pregnancy, and gestational diabetes. For purposes of the study, miscarriage is defined as the delivery of a liveborn fetus or a fetus who experienced fetal death for any cause before 20 + 0 weeks’ gestation. A miscarriage is considered early if delivery occurs at < 14 + 0 weeks and late if it occurs at ≥ 14 + 0 weeks’ gestation. Stillbirth is defined as fetal death before delivery after 20 weeks’ gestation [50]. Preterm birth is defined as delivery of a liveborn or stillborn infant for any reason between 22 + 0 and 36 + 6 weeks’ gestation [51]. Spontaneous preterm birth is defined as delivery that occurs after spontaneous onset of preterm labor or premature rupture of the membranes (PROM) or fetal membrane prolapse. Preterm labor is defined as spontaneous uterine contractions before membrane rupture, documented cervical change of at least 1 cm dilation or effacement during the admission, or dilation > 2 cm or effacement > 80% on admission for contractions. PROM is defined as spontaneous rupture of the membranes before the onset of contractions, regardless of subsequent labor augmentation or cesarean delivery. Indicated preterm birth is defined as delivery after induction or cesarean delivery between 20 + 0 and 36 + 6 weeks’ gestation for obstetric, maternal, or fetal indications. The indication for the delivery will be recorded. A birth is considered spontaneous unless documented otherwise. Term birth is defined as delivery of a liveborn or stillborn infant for any reason at ≥ 37 + 0 weeks’ gestation.

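### Preterm birth starts at 22+0 weeks but its indicated subtype starts at 20+0, and live births at 20+0 to 21+6 have no main outcome category

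*Protocol article*

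**What the plan says.** All the definitions stand in one paragraph of the Outcomes section of the protocol article.

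- Miscarriage includes liveborn fetuses and has a fixed upper limit: "miscarriage is defined as the delivery of a liveborn fetus or a fetus who experienced fetal death for any cause before 20 + 0" weeks.
- Stillbirth requires death in utero: "Stillbirth is defined as fetal death before delivery after 20 weeks" of gestation.
- Preterm birth is "delivery of a liveborn or stillborn infant for any reason between 22 + 0 and 36 + 6" weeks.
- The indicated subtype has a different lower limit: "Indicated preterm birth is defined as delivery after induction or cesarean delivery between" 20+0 and 36+6 weeks.
- Spontaneous preterm birth is defined by how the delivery began (preterm labor, membrane rupture or membrane prolapse) and carries no gestational-age limit. The definitions of preterm labor and membrane rupture on which it rests carry none either.
- Term birth starts at 37+0.
- A birth with no documented type of onset is treated as spontaneous.

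The same section lists preterm birth and pregnancy loss among the maternal outcomes, and miscarriage and stillbirth among the primary fetal/newborn outcomes. It names gestational age at birth as the primary outcome of the study.

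**The concern.** A subtype should lie inside the outcome that it divides, and the classes of pregnancy ending should leave no interval uncovered. Neither holds between 20+0 and 21+6. The indicated subtype reaches two weeks below preterm birth. Miscarriage, which takes in live deliveries, stops at 20+0, while the next class open to a live delivery begins at 22+0.

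Two things are at stake. First, spontaneous and indicated preterm births need not add up to total preterm births. Second, a live delivery at 19+6 is a pregnancy loss and one at 22+0 is a preterm birth, but one in between is neither. The section on challenges and anticipated responses suggests combining stillbirth and miscarriage into one fetal-death outcome. Under the printed definitions, that composite would include live deliveries before 20+0 and omit those at 20+0 to 21+6.

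Participants are under observation in this window, since the Recruitment section allows enrollment up to 20+6. Charts are abstracted by staff certified locally at each site, so an unclear rule can be applied differently from site to site.

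**Working it through.** The plan gives no figure to reproduce. The check is whether the definitions nest and cover every delivery. All limits come from the Outcomes section and are converted to days as 7 × weeks + days.

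| Class | Stated limits | Days | Live births included? |
|---|---|---|---|
| Miscarriage | before 20+0 | up to 139 | yes |
| Stillbirth | after 20 weeks (read as from 20+0) | 140 onward | no |
| Preterm birth | 22+0 to 36+6 | 154 to 258 | yes |
| Indicated preterm birth | 20+0 to 36+6 | 140 to 258 | yes |
| Spontaneous preterm birth | none stated | – | yes |
| Term birth | 37+0 or later | 259 onward | yes |

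The lower limits of preterm birth and its indicated subtype differ by 154 − 140 = 14 days, that is days 140 to 153, or 20+0 to 21+6.

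Each kind of delivery in that window classifies as follows. For the spontaneous subtype there are two readings: it takes the 22+0 limit of preterm birth, or it has no lower limit.

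| Delivery at 20+0 to 21+6 | Main class | Subtype |
|---|---|---|
| Live, indicated | none | indicated preterm birth |
| Live, spontaneous | none | none with the 22+0 limit; spontaneous preterm birth with no limit |
| Fetal death, indicated | stillbirth | indicated preterm birth |
| Fetal death, spontaneous | stillbirth | none with the 22+0 limit; spontaneous preterm birth with no limit |

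Three results follow.

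1. Every indicated delivery in the window, live or dead, is in the indicated subtype and not in preterm birth. Both limits are given to the day.
2. Every live birth in the window is outside all four main classes, on either reading. Only the spontaneous live birth can be outside every category, and only if the 22+0 limit is read in.
3. Reading no limit into the spontaneous subtype does not help. A spontaneous delivery at 18+0 would then be both a miscarriage and a spontaneous preterm birth.

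From 22+0 to 36+6 the definitions nest properly.

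On size, the Statistical analysis section expects about 180 preterm births. One live birth moved into or out of that count changes it by 1/180, about 0.6%. The document gives no rate of live birth at 20+0 to 21+6, so the number of such births cannot be derived.

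**The case against.** The strongest reply is that this is a wording mismatch in a condensed article with almost no consequence. Much of that stands. The primary outcome is gestational age as a continuous variable, and a live birth at 21+0 has a value there. Only total preterm births are counted in the Statistical analysis section, and no separate spontaneous or indicated analysis is announced. The article refers to a manual of operations and an operationalized abstraction protocol, neither of them shown, which may already settle the coding.

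One could also read the definitions as nested, so that an indicated preterm birth must first be a preterm birth. That would remove the subtype problem, but only by overriding a limit that the text prints explicitly. It would also take indicated live births at 20+0 to 21+6 out of the one category they now have. An unseen manual may guide abstractors but does not cure definitions that the article gives as those of the study.

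A reader might go further and infer that the most severe early deliveries vanish from the loss and preterm outcomes, are counted as non-cases, and so bias results toward no effect. The document does not support this. Fetal deaths in the window, including an induction for fetal death, are stillbirths and stay in the loss outcome. Nothing says that the unclassified live births enter an analysis as non-cases. They are not term births, so a comparison with term births would exclude them. Nor is it sound to set all deliveries in the window against the 11 expected stillbirths, because the fetal deaths among them are already stillbirths.

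**Conclusion.** The definitions are inconsistent as printed, and nothing elsewhere in the article reconciles them. The indicated subtype extends 14 days below preterm birth, and live births at 20+0 to 21+6 have no main class. This needs no outside figure. It rests only on the stated limits and on reading stillbirth as starting at 20+0.

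The impact is small. It is confined to live births in the window for the preterm and pregnancy-loss outcomes, and to all indicated deliveries in the window for the spontaneous/indicated split. The live births are probably few, though that is a judgement because no rate is given. The primary analysis of gestational age is not affected. Since the handling of these births is not stated, no direction of bias can be claimed.

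**What to change.** Reconcile the definitions in the Outcomes section in three steps.

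- Use one lower gestational-age limit for preterm birth and for both subtypes, and state that spontaneous and indicated preterm births lie within total preterm birth and sum to it.
- Assign live births at 20+0 to 21+6 to one named category. If the common limit is 20+0, they are preterm births. If it is 22+0, they go to a pregnancy-loss category. Either choice closes the gap, and the document does not determine which the investigators intended.
- Put the same rule into the chart-abstraction instructions and the re-abstraction checks at all sites.

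The cost is a few lines of wording, one abstraction code and possibly the recoding of a few charts already abstracted. No new data are needed.

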## Methods

### Recruitment

Hospitals located in one of the 13 Heartland Study region states (Arkansas, Illinois, Indiana, Iowa, Kansas, Michigan, Minnesota, Missouri, Nebraska, North Dakota, Ohio, South Dakota, or Wisconsin) will be recruited as affiliated clinical sites. Currently participating clinical sites include Indiana University School of Medicine- affiliated Hospitals in Indianapolis, Indiana; Franciscan Health Center in Indianapolis, Indiana; and Gundersen Lutheran Medical Center in La Crosse, Wisconsin, and University of Iowa in Iowa City, Iowa. Pregnant persons attending obstetric clinics affiliated with a clinical site hospital will be recruited, although other pregnant peopleliving in Heartland Study states are also eligible to participate.

The target enrollment is 2000 pregnant dyads. To evaluate the distribution of herbicide concentrations among Midwestern pregnancies, a target of 30% of participants will be recruited from rural areas, categorized as those areas outside of urban area centers according to US census designations [43]. Pregnant persons ages 18 or older at time of recruitment who are being seen at prenatal clinics and who are ≤ 20 + 6 weeks gestation will be recruited. Best clinical estimate of gestational age will be utilized for recruitment purposes [44]. Both singleton and twin pregnancies will be included. The other putative biological parent will also be invited to enroll as a secondary participant, subject to the primary participant’s consent. Exclusion criteria include the primary participant not being fluent in and/or able to fully understand, read, write, or speak the English or other approved languages, or inability to provide written informed consent. Trained study personnel will screen for eligibility, explain the study purpose and protocol, and administer informed consent. Approval for the Heartland Study protocol and procedures will be obtained from each clinical site hospital’s local governing Institutional Review Board. If materials are developed in other languages, such as Spanish, persons who are able to fully understand, read, write, or speak those languages will be eligible for enrollment.

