Hypertensive disorders of pregnancy include gestational hypertension, preeclampsia, eclampsia, and HELLP [hemolysis, elevated liver enzymes, and low platelet count] syndrome [52]. Gestational hypertension is defined as systolic blood pressure over 140 mmHg or diastolic blood pressure over 90 mmHg measured on at least two occasions 4 or more hours apart after 20 weeks’ gestation in a pregnant person that previously had normal blood pressure. Pre-eclampsia is gestational hypertension with proteinuria (300 mg or more in a 24-h urine collection, or other relevant clinical measurement). HELLP Syndrome and eclampsia are severe features of pre-eclampsia. HELLP Syndrome includes symptoms of Hemolysis, Elevated Liver Enzymes, and Low Platelet Count. Eclampsia is the manifestation of neurologic symptoms precipitated by hypertension. Diagnoses of these conditions made by a provider based on other clinical indications are also included.

Gestational diabetes is defined as a fasting plasma glucose ≥ 7.0 mmol/l (126 mg/ dl), a 2-h plasma glucose ≥ 11.1 mmol/l (200 mg/dl) following a 75 g oral glucose load, or a random plasma glucose ≥ 11.1 mmol/l (200 mg/ dl) in the presence of diabetes symptoms [53]. Additionally, gestational diabetes may be diagnosed clinically based on sequential screening with an abnormal 1 h glucose challenge test (50 g) followed by two abnormal values on a fasting 3-h glucose tolerance test, using appropriate cutoffs recommended by the American College of Obstetrics and Gynecology [54]. A participant is considered to have gestational diabetes if the criteria are documented or if a physician diagnosis of gestational diabetes is documented in the chart.

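### The gestational diabetes case rule has no new-onset condition and prior diabetes is not an exclusion, so diabetes that predates pregnancy can be counted as an outcome

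*Protocol article*

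**What the plan says.** In the protocol article, Outcomes, the definition opens with a threshold: "Gestational diabetes is defined as a fasting plasma glucose ≥ 7.0 mmol/l (126 mg/ dl"). It then lists a 2-hour value after a 75 g load, and "a random plasma glucose ≥ 11.1 mmol/l (200 mg/ dl) in the presence of diabetes symptoms". Two-step screening is a further clinical route. The paragraph ends with the operative rule: "A participant is considered to have gestational diabetes if the criteria are documented". The same sentence gives a recorded diagnosis by a physician as the alternative. The routes are joined by *or*, so a documented glucose criterion is sufficient by itself.

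The preceding paragraph of the same section defines gestational hypertension by readings taken "after 20 weeks’ gestation in a pregnant person that previously had normal blood pressure". That definition has both a time window and a prior-status condition.

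Under Recruitment, the exclusions begin "Exclusion criteria include the primary participant not being fluent" and go on to inability to consent. Diabetes is not mentioned. Under Study protocol, medical history is collected by questionnaire and by chart review. The list of potential confounders in Statistical analysis does not name diabetes.

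**The concern.** Gestational diabetes is one of the Phase 1 hypotheses and one of the secondary outcomes with a projected case count (126). Diabetes present before conception cannot be an effect of herbicide levels measured in prenatal urine. The printed rule nevertheless lets it count as an outcome, because a qualifying glucose value makes a case whatever the participant's earlier status.

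There are two kinds of misclassification. Prior diabetics with a qualifying value in the chart become false cases. Prior diabetics without one remain as non-cases, although they cannot develop the outcome. If prior diabetes is unrelated to exposure, false cases pull the odds ratio towards 1 and reduce the power to detect a real association.

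**Working it through.** **Reading the text.** Side by side, the two definitions differ as follows.

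| Condition | Gestational hypertension | Gestational diabetes |
|---|---|---|
| Time window in pregnancy | after 20 weeks | none stated |
| Previously free of the condition | required | none stated |
| Prior disease excluded at enrolment | not needed, given the clause | no |
| Prior disease among listed confounders | not needed, given the clause | no |

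The adjective *gestational* does not supply the missing condition, because it is part of the term being defined.

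**The plan's own figures** (Statistical analysis).
- Implied prevalence: 126 / 1,800 = 7.0%.
- Secondary type I error: 0.05 / 6 = 0.0083.
- Detectable odds ratio per SD, for a continuous exposure in logistic regression: exp[(z₁₋α/₂ + z₀.₈₀) / √(N·p·(1−p)·(1−R²))]. The 80% power is stated for the primary outcome and is assumed here for the secondary ones. R² is that of the exposure on the covariates, which the article does not give.
- For gestational diabetes with N = 1,800 and R² = 0: √(1,800 × 0.07 × 0.93) = 10.82, and exp(3.48 / 10.82) = 1.38. With R² = 0.20 it is 1.43.
- Over the five outcomes other than stillbirth, the range is 1.25 to 1.62 at R² = 0 and 1.28 to 1.71 at R² = 0.20. The latter rounds to the article's 1.3 to 1.7.

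These figures show that the stated power can be reproduced. They neither support nor refute the point, which rests on the wording of the definition.

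**Size of the effect.** Assumptions: a proportion q of participants are prior diabetics who are counted as cases, on top of the 126 true cases; their status is unrelated to exposure; the true odds ratio is 1.40 per SD. The share of false cases is f = 1,800q / (126 + 1,800q). The estimated odds ratio is approximately exp[(1 − f)·ln 1.40], with ln 1.40 = 0.3365. Power is Φ(b·√(N·p·(1−p)) − z₁₋α/₂), where b is the diluted log odds ratio, p = (126 + 1,800q) / 1,800 and R² = 0.

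| q wrongly counted | False cases | Share f | Estimated OR | Power |
|---|---|---|---|---|
| 0 | 0 | 0 | 1.40 | 84% |
| 0.5% | 9 | 9/135 = 6.7% | 1.37 | 81% |
| 1% | 18 | 18/144 = 12.5% | 1.34 | 77% |
| 2% | 36 | 36/162 = 22.2% | 1.30 | 71% |

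Here q is the proportion actually counted, not the prevalence of prior diabetes. If prevalence were 1% to 2% and half of those participants had a qualifying value, q would be 0.5% to 1% and the estimate 1.37 to 1.34. The dilution depends on q and the 7% only, so it does not change with the number analysed. The effect of prior diabetics who stay as non-cases is not included.

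**The case against.** The strongest reply is that the article condenses a fuller document. It mentions a common protocol and a manual of operations, and says that abstractors are certified on an operationalised protocol. The exclusion sentence uses a verb that need not introduce a complete list. The definition also cites sources that are not shown. A rule on prior diabetes could sit in any of these. That lowers confidence that prior diabetics will in practice be counted. It does not remove the point: the article prints this case rule in full, down to thresholds and glucose loads, and gives the neighbouring outcome the condition that this one lacks.

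A reader might infer that every known diabetic is counted as a case, or is counted from the first visit. The text does not support that. Counting needs a listed value, an abnormal two-step screen or a chart diagnosis of gestational diabetes; outcomes come from chart review; and no section says that glucose is measured at the first visit. A reader might also infer reverse causation, through diabetics eating differently. The study measures diet as a route of exposure, but nothing in the document says that diet differs by diabetes status, and the calculation above assumes no link.

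Finally, the primary outcome definition, gestational age at birth, is untouched, and the error can be corrected at analysis from data already collected. Both are true and bear on the priority of the point.

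**Conclusion.** The point holds as a defect in the stated outcome definition. Under the printed rule, diabetes before pregnancy can be classified as gestational diabetes, and prior diabetics who are not so classified stay in a denominator to which they do not belong.

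The size is uncertain because the documents give no prevalence. With 0.5% to 2% of participants wrongly counted, and no relation to exposure, a true odds ratio of 1.40 falls to about 1.37 to 1.30. At 0.5% this is a small change. At an assumed prevalence of 2%, the figure of 1.30 is an upper bound on the harm, since it needs every prior diabetic to meet a criterion. Comparison with the detectable odds ratio should be made with care, because that figure is 1.38 or 1.43 at N = 1,800 depending on an R² that the article does not give for these models.

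One secondary outcome is affected. The change should be made because the contrast with gestational hypertension is plain and correction is cheap, not because the study's main conclusion is at risk.

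**What to change.** Add to the gestational diabetes definition a condition such as *in a participant without diabetes before pregnancy*, mirroring the hypertension clause. For the gestational diabetes analysis only, remove participants with diabetes recorded before pregnancy from both numerator and denominator, using the medical history already collected. Report how many were removed. If the manual of operations already contains such a rule, state it in the definition.

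The glucose thresholds and all clinical care stay as they are. The cost is one clause and, if prior diabetes is present in 1% to 2% of participants (an assumption), that fraction of the sample for this one secondary outcome: 18 to 36 of 1,800.

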### Data management and storage

Data will be housed in a REDCap database. Direct entry into the database via secure links will be available for participants. Data collected at visits and chart abstraction will be entered by study staff. The Heartland Study REDCap database will be maintained at Indiana University and the data will undergo regular quality control checks and cleaning. When ready for analysis, the data will be securely transmitted to the study statistical analysis team.

A Data Coordinating and Analytics Core, housed at Indiana University School of Medicine, is responsible for data monitoring and quality control. Regular reports and data queries are made to study sites to ensure data accuracy. A study monitor with regulatory experience is performing study data monitoring and regulatory compliance regularly throughout the study and making site visits for document and data verification.

## Statistical analysis

The Heartland Study is designed as a prospective cohort study with target recruitment of 2,000 pregnancies. Anticipated loss to follow-up is estimated at conservatively estimated at 20%, yielding approximately 1,800 analyzable maternal-infant dyads for the longer-term Phase 2 portion of the study. Based on prevalence estimates reported in prior studies [55–60], it is estimated that this will yield (all approximated) 180 preterm births, 288 cases of hypertensive disorders of pregnancy, 126 cases of gestational diabetes, 90 cases of fetal growth restriction, 54 cases of congenital anomalies/malformations, and 11 cases of stillbirth. The detectable R^2^ attributed to the herbicide exposure variable of interest from a multiple regression model fit to the primary outcome (gestational age) adjusting for 5 covariates (with combined R^2^ of 0.20 by covariates themselves), with 80% power and a type I error of 0.05, is 0.003. The detectable odds ratios for presence of secondary outcomes associated with a one standard deviation increase in the herbicide exposure variable of interest range between 1.3 and 1.7 (excluding stillbirth), with type I error set at 0.0083 to keep familywise error at 0.05 for secondary outcomes [61]. Thus, the study is powered to detect several meaningful associations between herbicide exposures of interest and pregnancy outcomes.

Descriptive statistics, including appropriate parametric and semiparametric methods, will be used for continuous, binary, ordinal, and polytomous variables to describe characteristics of the cohort, exposures, and outcomes. We will examine the concentration data for appropriateness of cutoff values (quartiles, quintiles, high/low, etc.) or use as a continuous variable. Examples of statistical modeling approaches that we intend to utilize include least-squares linear regression, which will be used to describe the unadjusted associations between continuous outcomes (e.g., length of gestation or birthweight) and longitudinal exposure variable; and logistic regression, which will be used to describe the unadjusted association between a dichotomous outcome (e.g., diagnosis of pre-eclampsia or gestational diabetes, presence of congenital anomaly) and longitudinal exposure variables. Multivariate models will also be fit using suitable stratification and modeling adjustments for confounding and assessments of effect modification to evaluate associations between each outcome and multiple longitudinal exposures using methods appropriate to the structure of the data and analyses [62]. We will begin with simple multiple logistic regression models but will adjust to other appropriate models based on the data. To evaluate for the presence of exposure misclassification, an exposure matrix variable utilizing both biomarker and geospatially derived exposure estimates will be modeled with respect to each outcome [63].

Confounding variables have been determined a priori based on prior studies. Potential confounding factors to be considered are maternal age [64, 65], country of birth [66, 67], race/ethnicity [68, 69], height and preconception weight (including Body Mass Index) [70, 71], pregnancy weight gain [72, 73], marital status [64, 74], employment status [75, 76], socioeconomic status [77, 78], education level [78, 79], smoking status [80, 81], insurance coverage [82–84], alcohol use [85, 86], drug use, caffeine use [87], history of fetal loss and gestational age at loss [88], parity [89, 90], prenatal care [91], and rurality [92, 93]. As we will have residential address information, we will be able to explore the impact of location-based markers of social determinants of health such as distance to health care facilities, area deprivation, green space, and others.

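### A 20% loss from 2,000 recruits leaves 1,600, not the 1,800 on which all six expected case counts are based

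*Protocol article*

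**What the plan says.** The Statistical analysis section describes a "prospective cohort study with target recruitment of 2,000 pregnancies"; the Recruitment section agrees ("The target enrollment is 2000 pregnant dyads"). The loss sentence then reads "Anticipated loss to follow-up is estimated at conservatively estimated at 20%, yielding approximately 1,800 analyzable maternal-infant dyads", and it goes on to assign those dyads to the longer-term Phase 2 part of the study.

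The next sentence says that this number will produce "180 preterm births, 288 cases of hypertensive disorders of pregnancy, 126 cases of gestational diabetes, 90 cases of fetal growth restriction", followed by 54 congenital anomalies and 11 stillbirths, all marked as approximate.

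For the primary outcome, gestational age, the detectable R² for the exposure, with five covariates that themselves explain 0.20 and "with 80% power and a type I error of 0.05, is 0.003". For the secondary outcomes other than stillbirth, the detectable odds ratio per standard deviation of exposure is given as 1.3 to 1.7 at a type I error of 0.0083. No sample size is attached to the R² or to the odds ratios. The paragraph concludes that the study is adequately powered for several associations.

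**The concern.** This one paragraph is the article's whole justification of study size, and its loss rate and analysable number cannot both be right. The error carries forward, because the expected case counts are built on the larger number and the power conclusion follows from the paragraph.

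There is a second fault in the same place. The base of 1,800 is labelled as the Phase 2 set, but preterm birth, hypertensive disorders, gestational diabetes, growth restriction, anomalies and stillbirth are pregnancy and birth outcomes. The section on the design of the study places these in Phase 1 and says that the report covers Phase 1. Phase 2 concerns early childhood development, to which a stillbirth cannot contribute. Changing 20% to 10% would repair the subtraction but not this label.

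**Working it through.** **Inputs, all from the Statistical analysis section:** 2,000 recruited; 20% loss; about 1,800 analysable; the six case counts; five covariates with combined R² of 0.20; alpha 0.05 and 80% power for the primary outcome; alpha 0.0083 for the secondary outcomes. Three inputs are assumed: two-sided tests, 80% power for the secondary outcomes, and the share of exposure variance explained by the covariates (ρ²), which is varied from 0 to 0.2.

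**1. Retained number.**
- 2,000 × (1 − 0.20) = 1,600.
- 1 − 1,800/2,000 = 0.10, so 1,800 is a 10% loss.
- Dividing by 1.2 does not give 1,800 either: 2,000/1.2 = 1,667.
- Keeping 1,800 after a 20% loss needs 1,800/0.80 = 2,250 recruits.

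**2. Base of the case counts.** Dividing each count by 1,800 gives round percentages, so 1,800 is the base. The other columns apply the same percentages to 1,600 and 2,000.

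| Outcome | Stated | Share of 1,800 | At 1,600 | At 2,000 |
|---|---|---|---|---|
| Preterm birth | 180 | 10% | 160 | 200 |
| Hypertensive disorders | 288 | 16% | 256 | 320 |
| Gestational diabetes | 126 | 7% | 112 | 140 |
| Fetal growth restriction | 90 | 5% | 80 | 100 |
| Congenital anomalies | 54 | 3% | 48 | 60 |
| Stillbirth | 11 | 0.6% | about 10 | about 12 |

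Relative to 1,600, the stated counts are too high by 1,800/1,600 − 1 = 12.5%.

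**3. Detectable R², primary outcome.** Noncentral F test of one exposure term given five covariates, with effect size f² = R²/(1 − 0.20 − R²), noncentrality N·f² and N − 7 denominator degrees of freedom. A close approximation is R² ≈ (1.960 + 0.842)² × 0.80/N = 6.28/N.

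| N | Approximate | Exact | Rounded |
|---|---|---|---|
| 2,000 | 0.0031 | 0.0031 | 0.003 |
| 1,800 | 0.0035 | 0.0035 | 0.003 (0.00348 before rounding) |
| 1,600 | 0.0039 | 0.0039 | 0.004 |

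The stated 0.003 is therefore reproduced at 1,800 or 2,000, but not at 1,600. For the effect detectable with 80% power at 1,800 (R² about 0.0035), power at 1,600 is about 75%.

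**4. Detectable odds ratios, secondary outcomes.** OR = exp{[z(1 − 0.0083/2) + z(0.80)] / √[N·p·(1 − p)·(1 − ρ²)]}. The range runs from the commonest outcome (p = 0.16) to the rarest one kept (p = 0.03).

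| N | ρ² = 0 | ρ² = 0.1 | ρ² = 0.2 |
|---|---|---|---|
| 1,600 | 1.27–1.67 | 1.28–1.71 | 1.30–1.77 |
| 1,800 | 1.25–1.62 | 1.27–1.66 | 1.28–1.71 |
| 2,000 | 1.24–1.58 | 1.25–1.62 | 1.27–1.67 |

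The stated 1.3 to 1.7 is matched at 1,600 with ρ² of 0 or 0.1, at 1,800 with 0.1 or 0.2, and at 2,000 with 0.2. It does not identify the N that was used.

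**The case against.** The best defence is that the article does not show which figure is the slip. If 10% was intended, the counts and R² are right. If the loss applies only to Phase 2 and nearly all 2,000 pregnancies contribute birth outcomes, the counts are slightly too low and 0.003 is right. The counts are marked as approximate, and the Challenges section already concedes low power for rare outcomes. This stands as far as it goes: any overstatement is conditional. It does not remove the contradiction. A gap of 200 is half of the stated loss, too much for rounding to absorb. The target is 2,000 throughout; the Challenges section says at least 2,000 but names no larger figure.

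A reader might infer more than the document supports:

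- **That the detectable effects are overstated.** The direction is the reverse. A smaller N raises the smallest detectable effect, so at 1,600 the stated R² would be too small and the power too optimistic. Nor does that R² depend on the case counts; it follows from N.
- **That the odds ratios should read about 1.3 to 1.8.** That needs N = 1,600 together with ρ² = 0.2. The 0.20 in the article is the covariates' R² for gestational age, not for exposure. With ρ² of 0 or 0.1, 1,600 gives the stated range.
- **That primary power is only 69%.** This is the power at 1,600 for an R² of exactly 0.003. It treats a figure given to one significant digit as exact; on that reading even 2,000 gives 78% and 1,800 gives 74%. The like-for-like fall is from 80% to about 75%.
- **That the lack of a separate Phase 1 number is itself an error.** A condensed article may leave that to the full protocol. The point here is narrower: the base used for Phase 1 counts carries a Phase 2 label.

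**Conclusion.** The paragraph is wrong as written: 20% loss from 2,000 and 1,800 analysable dyads contradict each other, and nothing elsewhere in the article resolves it. The consequence depends on which figure was intended.

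- **20% meant, and applied to the analysed set:** all six counts are 12.5% too high, the detectable R² becomes 0.004, and about 5 points of power are lost for the primary outcome.
- **10% meant:** only the loss figure is wrong.

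Under either reading, the Phase 2 label on the base for Phase 1 outcomes still needs correcting.

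The R² result assumes a two-sided test, as is usual for an F test; the article does not state sidedness. A one-sided 5% test would give 0.0031 at 1,600, so the mismatch in R² rests on that assumption. The mismatch between the loss rate and 1,800 does not.

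The practical effect is modest. The calculations do not show that the study is inadequately powered, or that the odds-ratio range is wrong.

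**What to change.** Choose one loss rate and make the rest of the paragraph follow from it:

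- **If 20% is kept:** 1,600 analysable; about 160, 256, 112, 80, 48 and 10 expected cases in the order listed; detectable R² of 0.004.
- **If 10% was meant:** change the loss figure and keep 1,800, the present counts and 0.003.

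In both cases, say which phase the loss applies to, base the Phase 1 counts and detectable effects on the Phase 1 number, and give that number beside the R² and the odds ratios. Recompute the odds ratios from it, with the assumed exposure–covariate correlation stated, and do not replace them with 1.3 to 1.8.

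The cost is a text correction. If 20% stands, the published figures become slightly less favourable; recruitment and the planned analyses need not change.
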